## Abstract

**Background:**

Research shows that more than half of the people taking medication for a chronic condition are non-adherent. Nonadherence hinders disease control with a burden on patient quality of life and healthcare systems. We developed a tool that provides insight into nonadherence risks and barriers for medication-adherence including an intervention strategy to overcome those barriers. This study aims to assess the effectiveness of using this adherence tool in starters with cardiovascular or oral blood glucose-lowering medication to improve medication-adherence.

**Methods/design:**

In a cluster-randomized controlled trial 25 pharmacies in the Netherlands will be randomized to the intervention or control arm. Patients registered in a general practice participating in a collaborative can be included when they start cardiovascular or oral blood glucose-lowering medication prescribed by their general practitioner.

Participants complete an assessment consisting of measuring nonadherence risk and potential barriers to adherence. For patients with an increased nonadherence risk, a graphic barrier profile is created, showing to what extent eight cognitive, emotional, or practical barriers are present.

All patients will fill in the medication-adherence assessment twice: between 1 and 2 weeks after the start of the medication and after 8 months.

The intervention strategy consists of discussing this barrier profile to overcome barriers. Pharmacists and assistants of the intervention pharmacies are trained in discussing the profile and to offer a tailored intervention to overcome barriers. In the control arm, patients receive care as usual.

The primary outcome is medication-adherence of patients with a high risk of nonadherence at 8 months follow-up.

Secondary outcomes include the difference in the percentage of patients with an increased nonadherence risk between intervention and control group after 8 months, the predictive values of the baseline questionnaire in the control group in relation to medication-adherence after 8 months, medication-adherence after 1 year follow-up, and barriers and facilitators in the implementation of the tool.

**Discussion:**

This manuscript presents the protocol for a cluster-randomized clinical trial on the use of an adherence tool to improve medication-adherence. This study will provide insight into the effectiveness of the tool in starters with cardiovascular or oral blood glucose-lowering medication in improvement of medication-adherence.

**Trial registration:**

The Netherlands National Trial Register, NTR5186. Registered on 18 May 2015.

**Electronic supplementary material:**

The online version of this article (doi:10.1186/s13063-016-1393-2) contains supplementary material, which is available to authorized users.

## Background

Adherence to chronic medication is problematic in clinical practice. Nonadherence leads to poor disease control with a burden on patient quality of life and healthcare systems [1]. Research shows that, on average, 50 % of patients with a chronic condition are not adherent, with adherence estimates ranging from 17 to 80 % [2–4]. Drugs for asymptomatic chronic conditions are found to have especially low adherence rates [5]. In several studies, the risk for nonadherence was shown to be highest in the first year after the start with chronic medication [6, 7]. Consequently, interventions to warrant adherence are expected to be most effective at the initiation of a chronic medication treatment.

Various causes have been demonstrated to hamper adherence [4, 8]. Conventional models distinguish between intentional and nonintentional barriers as causes for poor adherence [9]. Intentional barriers develop because of patients’ beliefs and perceptions about their medications and diseases. These barriers can be further subdivided into cognitive and emotional barriers. Nonintentional barriers depend on capacity, resources, and practical barriers [10]. Besides personal beliefs, adherence depends on the type of disease but may also vary within patients over time [10]. The multifaceted nature of the adherence problem illustrates that improving adherence is complex and needs interventions tailored to the individual patient [9]. A recent Cochrane review showed that current methods of improving medication adherence for chronic health problems are mostly complex and not very effective [11]. The effectiveness of nonadherence interventions can be improved by targeting the underlying barriers related to nonadherence for a specific patient. Interventions can focus on cognitive and emotional barriers (intentional nonadherence) or on practical barriers (nonintentional nonadherence), each with their own specific intervention ingredients tailored to patients’ needs. Depending on the character of the intervention, different primary healthcare providers can be involved. For instance, the pharmacist may be better equipped to implement aids to overcome practical barriers, and general practitioners (GPs) and nurses may be better able to help the patient overcome cognitive and emotional barriers. Though there are several instruments assessing actual medication adherence and various programs to improve adherence, at present, no tool is available for healthcare providers to predict the risk and potential causes for nonadherence at the start of chronic medication with a tailored approach to overcome the individual barriers detected. Such a tool would enable them to address potential barriers to nonadherence and prevent early cessation of chronic medication. Therefore, a predictive tool is needed at the start of chronic medication to assess the risk of future nonadherence and to address the assessed causes of the nonadherence for a patient at high risk.

Furthermore, an implementation strategy is needed to provide tailored interventions in primary healthcare settings. For the efficient implementation of effective interventions in existing primary healthcare workflows, a good cooperation between pharmacists, GPs, practice nurses, and assistants is required. Technology-based systems that enable easy communication between healthcare providers about the progress of interventions and agreement about the allocation of time and resources need to be in place.

At Philips Research, a questionnaire was developed that creates a barrier profile based on an online assessment. The questionnaire consists of two parts: the Probabilistic Medication Adherence Scale (ProMAS), which is an 18-item questionnaire to assess nonadherence risk [12], and an additional 23 questions that assess the underlying barriers related to nonadherence. The resulting barrier profile provides insight into the extent to which eight cognitive, emotional, and practical barriers may hamper a patient’s adherence. For each of the identified barriers, a set of recommendations was formulated in a manual for healthcare providers on how to address the barriers in an intervention. Consequently, in patients starting chronic medication and at high risk for nonadherence, as assessed by ProMAS, the barrier profile provides an intervention strategy to overcome cognitive, emotional, and practical barriers to adherence at an early moment and thereby promotes adherence.

The primary objective of this study is to assess the effectiveness of using the medication-adherence tool in starters with cardiovascular medication, which includes antiplatelets, antihypertensives, and lipid-lowering drugs (Appendix), and oral blood glucose-lowering medication in the improvement of medication adherence as measured by pharmacy dispensing data. A second objective is to evaluate the implementation strategy to reduce barriers identified in patients at risk for nonadherence for a primary care setting relating to the acceptability of the workflow for all stakeholders (pharmacists, general practitioners, and patients).

The primary research question is as follows:What is the benefit of using the medication-adherence tool for medication adherence of patients starting with cardiovascular or oral blood glucose-lowering medication identified as being at high risk for nonadherence at a follow-up of 8 months compared to usual care?

Secondary questions are as follows:a) What is the association between the ProMAS score at 8 months and the adherence after 8 months?b) To what extent can the identified barriers at 8 months predict medication adherence after 8 months?What are the predictive values of the ProMAS score and the barrier profile, measured at drug initiation, in relation to medication adherence after 8 months for all patients in the control group who started with cardiovascular of diabetes medication?What is the adherence of the subgroup of patients with a longer follow-up period of at least 1 year after drug initiation?

Process evaluations will address the following question:What are the barriers and facilitators, as experienced by pharmacists and patients, regarding the implementation of the medication-adherence tool in their daily practice?

The aim of this study protocol is to describe the design and methods of a study to assess the effectiveness of using a medication-adherence tool in starters with cardiovascular or oral blood glucose-lowering medication to improve medication adherence.

## Methods/design

### Study design

This study is a cluster-randomized trial with an intervention group of pharmacies (using the adherence tool) and a control group of pharmacies (providing usual care). The key components of the medication-adherence tool are described in Table 1.

**Table 1 Tab1:** Components of the medication-adherence tool

*■* Online questionnaire consisting of two parts
a) the Probabilistic Medication Adherence Scale (ProMAS), slightly adapted for use with patients with a first prescription of cardiovascular or oral blood glucose-lowering medication
b) assessment of the underlying barriers related to nonadherence
*■* Tools used by pharmacists to facilitate the provision of a tailored intervention
a) a 3-hour training session on patient-centered communication and discussion of the barrier profile
b) manual containing instructions for discussing and overcoming the various potential barriers for medication adherence
c) an internet-connected tablet to register new participants, to review the graphical barrier profile at the time of the second dispensing, and to make any notes regarding the conversation and applied intervention
*■* Tailored intervention

As the second dispensing, a tailored intervention is initiated for patients in the intervention group with an increased risk for nonadherence. All interventions start with a discussion of the patient’s barrier profile. The intervention will be tailored to the identified emotional, cognitive, and practical barriers of the patient.

As in daily practice, patients receive a new medication from their community pharmacist; therefore, the assessment of patients’ medication adherence and potential barriers was most appropriately situated in the community pharmacy for our study. In the Netherlands, patients with a first dispensing of a chronic drug usually receive only an amount for 2 weeks. Treatment is continued after 2 weeks according to the experiences of the patient. Thus, patients starting with the study medication will have to have contact with the community pharmacy within approximately 2 weeks. This makes it convenient to ask eligible patients to participate in the study at the first dispensing, let them fill in the medication adherence assessment before the second dispensing, and apply the intervention when necessary at the second dispensing. The feasibility of implementing the use of the adherence tool in the daily pharmacy workflow was piloted in two pharmacies. During the pilot period, researchers regularly contacted the pilot pharmacists in order to track their experiences and any developments and to solve any issues. After the pilot period, a meeting between the research team and the two pilot pharmacists was planned for evaluation of the pilot. Based on the experiences during the pilot period, workflow adaptations leading to an increase in convenience and efficiency were made. Small changes in study information for patients, pharmacists, and GPs were made after the pilot period.

For further clarification of this study protocol, we reference the study flow diagram (Fig. 1) and the SPIRIT checklist (Additional file 1).

**Fig. 1 Fig1:**
[figure not shown]
Flow diagram of the study

### Recruitment of pharmacies, general practices, and patients

The trial will be carried out with pharmacists, general practitioners, and their patients with a first prescription of cardiovascular medication, including antihypertensives, antiplatelets, and lipid-lowering drugs, or oral blood glucose-lowering medication made by their GP within the study period (see Appendix for drug classes and ATC codes). A first prescription is defined as no drug dispensing from a drug class issued to the patient in the preceding year. For example, a patient who used a beta-blocking agent in the preceding year is not eligible when starting another beta blocker but will be eligible when starting a statin.

The primary care cooperation De Ondernemende Huisarts (DOH), or The Innovative General Practitioner, will play a key role in the recruitment of pharmacies and general practices for this study. DOH is a general practice collaborative, i.e., approximately 70 GPs working in 16 group practices in the southeastern part of the Netherlands who that share an overarching management structure and develop and implement structured care for several prevalent chronic conditions, including cardiovascular diseases and diabetes.

#### Pharmacies

The DOH cooperates closely with a number of community pharmacies (so-called CaZo cooperation). In total, 25 pharmacies have joined the cooperative. A representative of DOH will contact all 25 pharmacies connected to the DOH cooperation and provide them an invitation and an information leaflet about the study. Three members of the research team will visit all pharmacists who express their intention to participate. After a detailed explanation of the study aims, methods, and expected outcomes to the pharmacists, written informed consent for both participation and collection of de-identified patient data from the pharmacist’s database will be obtained.

The participating pharmacies are randomized for the intervention or control group, which implies that the patients are clustered within pharmacies. Pharmacies are stratified into small or large depending on their number of patients registered with DOH GPs. After the randomization procedure (drawing from a hat by an independent research assistant and consecutive allocation) has been performed, the pharmacies will be informed of their assignment to either the intervention group or the control group. Only pharmacists and pharmacy assistants from the intervention group are being trained to interpret the barriers to adherence profile and to provide tailored care. This prevents contamination between the intervention and control patients. Because patients in the Netherlands predominantly visit one pharmacy for all their medication, pharmacists are assumed to have complete medication dispensing information for their patients [13].

Due to the test of the medication-adherence tool, both pilot pharmacies will have to participate in the intervention group.

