*■* Onsite support on the use of the tablet
*■* Availability of researcher for answering questions about the study
*■* Possibility to contact pilot pharmacist for questions and advice on study procedures

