### Sample size

For the sample size calculation, the following assumptions are made: we assume that a percentage of 60 % is nonadherent in our sample of patients at high risk based on their ProMAS score. This assumption is reasonable according to published studies [6]. We assume that the intervention will increase the 80 % PDC in the intervention group by 20 % compared to the control group. As patients are clustered within pharmacies, the evaluation will be performed by multilevel analysis to adjust for clustering. For the effect of clustering, an intracluster correlation (ICC) of 0.05 was assumed.

In agreement with conventional power calculations, a power of 80 % to detect a true difference and a chance of 5 % of a type 1 error to wrongly conclude on a difference are assumed. For this trial, in the DOH/CAZO setting, we assume that there are at least 14 community pharmacies willing to participate. The sample size calculation results in 39 patients needed per pharmacy. PASS software version 11 was used to determine the appropriate sample size. Considering 30 % lost to follow-up during the study period, 56 patients need to be included per pharmacy to achieve the power needed. If only 50 % of the patients agree to join the study, 112 patients need to be invited per pharmacy.

In the potentially participating 25 pharmacies, a total of at least 6,081 single patients with primary dispensings of cardiovascular or oral blood glucose-lowering medications were detected within 12 months (as observed in historical data). This means that, on average, 20 subjects started with cardiovascular or oral blood glucose-lowering medication monthly per pharmacy. Assuming 40 % of the starters at risk for nonadherence (determined by a ProMAS score ≥ 13), this means, on average, that eight patients are available monthly per pharmacy for an intervention. The period to have 112 starters on cardiovascular or blood glucose-lowering medication per pharmacy will be approximately 14 months.

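### The two pilot pharmacies are placed in the intervention arm without randomisation, and no analysis rule separates them from the randomised pharmacies

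*Protocol article*

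**What the plan says.** The Methods/design part of the abstract says that "25 pharmacies in the Netherlands will be randomized to the intervention or control arm". The Pharmacies section says the same of those that join: "The participating pharmacies are randomized for the intervention or control group", within strata of small and large pharmacies, by "drawing from a hat by an independent research assistant and consecutive allocation". The same section closes with an exception. Because they tested the tool, "both pilot pharmacies will have to participate in the intervention group".

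The Study design section explains their history: "The feasibility of implementing the use of the adherence tool in the daily pharmacy workflow was piloted in two pharmacies". The researchers were in regular contact with the pilot pharmacists during that period, and the workflow was changed in the light of their experience. In the implementation strategy (Table 3), pilot pharmacists also serve as a source of advice.

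The Data analysis section specifies an intention-to-treat primary analysis by multilevel model, adjusted for patient age, gender, diagnosis and number of medications. It does not mention the pilot pharmacies. The limitations in the Discussion cover contamination through general practitioners, the innovative setting and patient recruitment bias, but not this allocation.

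**The concern.** Randomisation protects a comparison only for units that could have gone to either arm. The two pilot pharmacies had no chance of being controls, so the control arm has no randomised counterpart for whatever is particular to them. What the article documents about them is practice with the tool before the trial and regular researcher contact during the pilot. Either could go with a different level of adherence support, and nothing is known about their underlying adherence.

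The unit of allocation is the pharmacy and the number of pharmacies is small, so two clusters carry real weight. Patient-level covariates cannot be relied on to remove a difference that arises at pharmacy level. The stated intention-to-treat principle does not help either: it compares clusters as randomised, and these two were not.

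**Working it through.** **Inputs from the Sample size section.** "we assume that a percentage of 60 % is nonadherent in our sample of patients at high risk", so 40% adherent in the control arm. The increase of 20 is read as percentage points (60% adherent under intervention). ICC 0.05, power 80%, type I error 5%, 39 evaluable patients per pharmacy. On the number of clusters, "we assume that there are at least 14 community pharmacies willing to participate". The abstract gives 25.

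**Assumptions not in the document.** 1:1 allocation, two-sided test, equal cluster sizes, and the pilots counted within the 14.

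**Step 1: reproduce the plan's figure.** Design effect = 1 + (39 − 1) × 0.05 = 2.9. The binomial variance is 0.4 × 0.6 = 0.24 in both arms.

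- Variance of one pharmacy's proportion = 0.24 × 2.9 / 39 = 0.01785.
- SE of the contrast, 7 v 7 = √(0.01785 × (1/7 + 1/7)) = 0.0714.
- Power = Φ(0.20/0.0714 − 1.96) = Φ(0.84) = 79.98%.

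The stated 39 per pharmacy is reproduced with unpooled variance. (Pooled variance gives 78.8% at 39.) The sample size arithmetic is not in question.

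**Step 2: weight of the pilots.** With 14 pharmacies, 2/7 = 29% of intervention clusters. With 25, 2/12.5 = 16%.

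**Step 3: shift and type I error.** Suppose adherence in the pilot pharmacies differs by x for reasons unrelated to treatment. With equal cluster sizes the contrast moves by (2/7)x or (2/12.5)x. With b = shift/SE, the two-sided type I error is Φ(−1.96 + b) + Φ(−1.96 − b). For 25 pharmacies, SE = √(0.01785 × 2/12.5) = 0.0534. The values of x are illustrative; no document figure supports any one of them.

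| x (points) | 14 pharmacies: shift | Type I error | 25 pharmacies: shift | Type I error |
|---|---|---|---|---|
| 5 | 1.4 | 5.5% | 0.8 | 5.3% |
| 10 | 2.9 | 6.9% | 1.6 | 6.0% |
| 20 | 5.7 | 12.6% | 3.2 | 9.2% |

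For scale, the between-pharmacy standard deviation implied by the plan is √(0.05 × 0.24) = 0.11, or 11 points. The last row therefore needs both pilots to lie about 20/11 = 1.8 standard deviations from the rest.

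**Step 4: cost of leaving the pilots out, at 39 per pharmacy.** The t column uses a noncentral t with (clusters − 2) degrees of freedom.

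| Clusters | SE | Power, normal | Power, t reference |
|---|---|---|---|
| 7 v 7 | 0.0714 | 80.0% | 73.0% |
| 6 v 6 | 0.0771 | 73.7% | 64.8% |
| 5 v 7 | 0.0782 | 72.5% | 63.6% |

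The 5 v 7 row applies if the pilots are simply removed from a 7 v 7 trial. The 6 v 6 row applies if the other 12 are randomised equally.

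**The case against.** The exception is disclosed, with its reason, in the section that describes randomisation, and the abstract's wording may be no more than compression. That is fair as far as it goes. It makes the abstract a matter of correction, but it leaves open how two non-randomised clusters are to be analysed. A separate analysis plan might hold such a rule. Even so, the article itself fixes the allocation and states an intention-to-treat analysis without qualification, so inclusion is the natural reading, although it is not said in so many words.

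A reader might infer more than the documents support:

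- **That the pilots are unusually motivated volunteers whose inclusion must inflate the effect.** The article does not say how they were chosen. Every participating pharmacy joins by consent, so volunteering does not set them apart. Their baseline adherence is not given. The regular researcher contact belongs to the pilot period; in the trial, all pharmacies receive a visit and have a researcher available.
- **That the type I error is 13%.** That is only the 20-point case with 14 pharmacies, where the assumed pilot difference equals the whole planned effect.
- **That exclusion takes power from 80% to 64–65%.** This compares a normal-formula figure with a t-based one. On the t basis the full 7 v 7 design is already at about 73%.
- **That advice from pilot pharmacists contaminates the controls.** Table 3 lists "Possibility to contact pilot pharmacist for questions and advice on study procedures". It does not say that skills in discussing barriers would reach control pharmacies.

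**Conclusion.** The concern holds as a point about allocation and analysis set. Two intervention clusters are not randomised, the article describes the pharmacies as randomised, and nothing in the stated analysis separates the two or adjusts at pharmacy level. The possible bias runs from slight to material across the illustrated range, and from about 29% to 16% of the arm is affected depending on how many pharmacies join. The direction is plausibly upward because of the pilots' prior experience, but it is not established. The defect does not depend on the direction.

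The shares and shifts rest on the assumptions listed with the inputs. The type I errors also hold the planned standard error fixed, whereas a fitted multilevel model would estimate the between-pharmacy variance from the data. The article does not say whether the pilots count towards the 14.

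**What to change.** 1. Define the primary comparison on the randomised pharmacies only.
2. Report the analysis including the pilot pharmacies as a labelled sensitivity analysis.
3. Keep the pilots in the process evaluation, where their experience is useful.
4. Correct the abstract and the Pharmacies section to say that all participating pharmacies except the two pilots are randomised.
5. State whether the pilots count within the 14, and restate the power for the randomised pharmacies.

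These are changes of wording and analysis set. The cost is in precision. If only 14 pharmacies join including the pilots, power at 39 per pharmacy falls from 80% to about 72–74% by the normal formula, or from about 73% to 64–65% with a t reference. If at least 14 of the 25 invited pharmacies are randomised besides the pilots, nothing is lost against the plan. The article assumes at least 14 willing pharmacies in all, so reaching that number cannot be taken for granted, and it is not a condition of the fix.
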